## Abstract

**Background:**

Obesity is a pressing public health concern, which frequently presents in primary care. With the explosive obesity epidemic, there is an urgent need to maximize effective management in primary care. The 5As of Obesity Management™ (5As) are a collection of knowledge tools developed by the Canadian Obesity Network. Low rates of obesity management visits in primary care suggest provider behaviour may be an important variable. The goal of the present study is to increase frequency and quality of obesity management in primary care using the 5As Team (5AsT) intervention to change provider behaviour.

**Methods/design:**

The 5AsT trial is a theoretically informed, pragmatic randomized controlled trial with mixed methods evaluation. Clinic-based multidisciplinary teams (RN/NP, mental health, dietitians) will be randomized to control or the 5AsT intervention group, to participate in biweekly learning collaborative sessions supported by internal and external practice facilitation. The learning collaborative content addresses provider-identified barriers to effective obesity management in primary care. Evidence-based shared decision making tools will be co-developed and iteratively tested by practitioners. Evaluation will be informed by the RE-AIM framework. The primary outcome measure, to which participants are blinded, is number of weight management visits/full-time equivalent (FTE) position. Patient-level outcomes will also be assessed, through a longitudinal cohort study of patients from randomized practices. Patient outcomes include clinical (*e.g*., body mass index [BMI], blood pressure), health-related quality of life (SF-12, EQ5D), and satisfaction with care. Qualitative data collected from providers and patients will be evaluated using thematic analysis to understand the context, implementation and effectiveness of the 5AsT program.

**Discussion:**

The 5AsT trial will provide a wide range of insights into current practices, knowledge gaps and barriers that limit obesity management in primary practice. The use of existing resources, collaborative design, practice facilitation, and integrated feedback loops cultivate an applicable, adaptable and sustainable approach to increasing the quantity and quality of weight management visits in primary care.

**Trial registration:**

NCT01967797.

## Background

Obesity is a common problem in primary care [1,2]. There are substantial direct and indirect costs to the healthcare system; conservative estimate of costs attributable to obesity in Alberta in 2005 totaled $1.27 billion [3]. Studies suggest that a primary care-based obesity treatment model could be cost-effective over the long term [2] and that treating obesity can reduce the incidence of a variety of chronic diseases [4-7]. However, obesity is ‘not effectively managed within our current primary health system’ [4-6]. To address this problem, a tool for obesity counseling and management in primary care settings, known as the 5As of Obesity Management™ has been developed [7]. This tool incorporates the conceptual structure of the Best Practices in Weight Management document, the Canadian Obesity Clinical Practice Guidelines [8], and the 5As methodological framework (Ask, Assess, Advise, Agree, Assist) [9]. Preliminary evidence shows that use of the 5As of Obesity Management can increase provider-client interactions in weight management [10]. However, the 5As have not been evaluated in a system-wide implementation study.

The Primary Care Network (PCN) model in Alberta has a 10-year history of embedding multidisciplinary teams in pre-existing family physician clinics. Chronic disease nurses and nurse practitioners working in this multi-disciplinary setting (with family physicians, mental health workers and dieticians) present a good model to target and assess improvement in obesity management.

The goal of this project is to implement and evaluate the 5AsT team intervention aimed at changing provider behaviour with regard to obesity management. This intervention, informed by the theoretical domains framework for behaviour change and the conceptual framework of complex innovation implementation, is co-developed with end-users, emphasizing bidirectional knowledge transfer among multidisciplinary team members to develop a pragmatic and sustainable approach to obesity management in primary care.

## Methods

### 5AsT study overview

The 5AsT trial is a theoretically informed, pragmatic randomized controlled trial with convergent mixed methods evaluation of an intervention on primary care providers to improve obesity management. Clinic-based multidisciplinary teams (RN/NP, mental health, dieticians) will be randomized to control or the 5AsT intervention group. The intervention providers will participate in biweekly learning collaborative sessions supported by internal and external practice facilitation. These learning collaboratives will explore provider-identified barriers to effective weight management in primary care. Evidence-based shared decision making tools will be co-developed and iteratively tested by practitioners. The primary outcome measure is the number of weight management visits per full-time equivalent (FTE) RN/NP position. This measure is longstanding, routine administrative data in the PCN. Participants are unaware of the primary outcome measure, and the research team is blinded to the result during the study period. Patient-level outcomes will be assessed, through a longitudinal cohort study of patients from randomized practices. Qualitative data will be collected from providers and patients, and evaluated using thematic analysis to understand the context, implementation and the effectiveness of the 5AsT intervention. Patient-level outcomes including clinical, health-related quality of life, and satisfaction with care will also be assessed.

Figure 1 provides an overview of the 5AsT trial, which consists of both a provider-level intervention study and a patient-level impact assessment. The 5AsT provider-level study is divided into three phases. Phase 1 is the ‘Intervention Phase,’ which consists of a kick-off session followed by bi-weekly two-hour learning collaborative sessions over six months. Phase 2 is the ‘Passive Phase,’ a six-month period where we provide no direct support to the 5As Teams but continue to collect data to determine if behavior change has been internalized. Phase 3 is the ‘sustainability phase,’ where the primary outcome measure continues to be collected over 12 months to determine if change can be sustained over time. The patient-level study will assess how patients coming from 5AsT intervention practices engage in weight management efforts over time compared to patients from control practices.

**Figure 1 F1:**
[figure not shown]
**5AsT study overview.** The upper portion pertains to the provider-level study and shows intervention and evaluation timeline. The lower portion pertains to the parallel patient-level study.

### Guiding theoretical frameworks

#### Conceptual framework of complex innovation implementation

Complex innovations such as behavioral change interventions in primary care can be conceived using this validated framework [11]. Our alignment with this framework reduces the chance that context change will negatively affect implementation or completion of the project. This framework informed the decision to have a clinical champion act as an internal practice facilitator from within the primary care network.

### Theoretical domains framework for behaviour change

The Theoretical Domains Framework is a validated, comprehensive overview of the core domains important to consider in behavioural change interventions in healthcare improvement [4]. This Framework informs our intervention on the practitioners to expand from knowledge alone, towards engaging in all components critical for their behaviour change. The 5AsT intervention leverages the clinical champion role for coaching and, the practice facilitation role to aid in logistical support, and the learning collaborative model to increase role identification, goal setting, identification of barriers and facilitators to action. We also used this framework to determine the target patient population. The patient study focuses on patients who have committed to action prior to recruitment (‘activated patients’), assessing their ability to initiate and sustain weight management efforts.

### Guiding evaluation framework: RE-AIM

Our overall evaluation summarized in Table 1, is guided by the RE-AIM framework: Reach into the target population; Effectiveness of the intervention; Adoption by target settings; Implementation including consistency and cost of delivery; and Maintenance of intervention effects over time (sustainability) [5,6,12,13].

**Table 1 T1:** RE-AIM framework as a guide for project evaluation

**Domain**	**Description**	**Measure for patients**	**Measure for providers**
**R**each	Degree to which target population is reached	• number recruited	• Control/intervention groups
		• percent attrition	• Intervention attendance
		• patient characteristics	• Provider-chosen topics (subject appropriateness)
**E**ffectiveness	Impact on study outcome	• SF 12	• Quantitative primary
		• BMI	outcome measure
		• 5AsT vs. non 5AsT patients	• Self-reported efficacy
**A**daptation	Organizational uptake	Not applicable	• Sustainability phase
			• Repeat provider interviews
**I**mplementation	Intervention implementation as intended	Not applicable	• Learning collaborative
			• Organizational by-in
			• Practice facilitation
			• Feedback loops
**M**aintenance	Can program outcomes be sustained over time?	• Longitudinal data collection	• Longitudinal data collection

### Setting/population

The 5AsT intervention was designed with our partner primary care network (PCN), which consists of 59 dedicated multidisciplinary healthcare providers (nurses, nurse practitioners, mental health workers, dieticians, exercise physiologists, respiratory therapists) embedded in 46 family practices with over 160 family physicians serving 192 655 Albertans. The PCN has been in a period of rapid growth.

At the practice level, the RN/NPs in the PCN are responsible for significant chronic disease management, including diabetes and weight management, as well as prenatal care.

To be eligible to be randomized to the intervention, PCN-affiliated family practice clinics must have joined the PCN by April 2013, and must have a multidisciplinary team including a nurse/nurse practitioner, mental health worker and a dietician affiliated with the clinic, resulting in 24 eligible clinic teams. The intervention unit is the PCN multidisciplinary team affiliated with the clinic, referred to as the ‘5AsT team.’

Patients are eligible to be recruited to the longitudinal cohort study if they declare activation for behaviour change through their enrolment and participation in one of the PCN programs for health (*e.g*., weight management groups, activity groups, mental health groups). These are run independently from the clinic-based 5AsT team. Patients are eligible regardless of what clinic they attend for their regular care.

### Intervention and control

The 5AsT intervention builds upon the knowledge product of the 5As of Obesity Management™ and extends it to a pragmatic, practice-based intervention for provider behaviour change. The 5AsT intervention will occur in biweekly learning collaborative sessions for six months. The content of the 5AsT learning collaborative sessions will be determined with the practitioners randomized to the intervention. The 5As teams will be supported by a 5As Champion, a recognized clinical leader in weight management from the PCN. This individual is identified and remunerated through the PCN and functions as an internal practice facilitator for the project. In addition to assisting the research team with coordinating their actions with the clinical operations of the PCN, the Clinical Champion serves as a coach and mentor to the 5AsT team members, and as a facilitator for the learning collaborative. Additional support to the 5AsT teams is provided by two external practice facilitators who identify resources, design prototype tools, collect feedback and coordinate with content experts, physicians, and graphic designers to refine the 5AsT tools.

Providers randomized to the control arm of the study all receive usual professional development courses for obesity management through Alberta Health Services and the PCN, which includes didactic training on the 5As of Obesity Management tool kit. Control providers will not take part in bi-weekly learning collaboratives, will not be given circulated learning materials, and will not receive added support from practice facilitators.

### Provider-level study

To test the effect of the 5AsT intervention, we will conduct a pragmatic, mixed methods, allocation concealed, randomized, blinded (outcome, data analysts), clinical trial. Figure 1 (upper) details the provider-level study.

### Hypotheses

1. Implementation of the 5AsT in primary care practice will increase the number of weight management visits per FTE conducted by the PCN RN/NPs. The primary outcome measure is the number of weight management visits as a function of provider full time equivalent (FTE) work (*i.e*., a half time nurse has an FTE of 0.5).

2. Implementation of the 5AsT in primary care practice will result in sustained changes in medical practice as evaluated by the RE-AIM framework [13,14].

### Qualitative primary question

What contextual factors affect the number of weight management visits conducted by the PCN practitioners?

### Allocation concealment and randomization

Following ethical approval and study registration, the eligible clinics (N = 24) were allocation concealed and randomized in a 1:1 ratio using a computer generated random sequence by a statistician external to the project. Randomization was stratified for larger vs. smaller patient panel sizes. Three strata with eight practices were created from the 24 eligible practice units. The first 8 units (Group 1) have panel size ≤2,754; Group 2 has clinic panel size from 2,755 to 6,576, and Group 3 has clinic panel size ≥6,577.

### Outcome ascertainment, blinding and equal treatment

The primary outcome measure is the number of weight management visits conducted by the RN/NP participants in their individual practices. Their practice involves many different kinds of clinical activities like prenatal visits, diabetes care, and other chronic disease management visits.

The primary outcome measure is a routine measure of clinical activity collected on standardized forms within the PCN at every clinical encounter; there is already an audit and quality assurance process in place for this measure. Due to the fact some provider participants work part time, or fractional FTE (full-time equivalent), this must be included in the primary outcome measure.

The provider subjects will be blinded to knowledge of the primary outcome measure so as not to influence their behavior in data collection. The research team will not be involved with the collection of the primary outcome measure. The investigators and health practitioners will have no access to this data and will remain blinded to the results until 12 months following implementation. Data analysts will remain blinded to the allocation of intervention versus control.

Aside from the 5AsT intervention programming, there is no difference in treatment between the intervention and control practitioners. The RN/NPs’ clinical practices are geographically dispersed and do not routinely interact.

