### Primary outcomes

Two stage summary statistics will be used for the analysis of the primary outcome; the number of weight management visits/FTE for each practitioner will be derived for each time point, and the average of the weight management visits/FTE for the intervention and the control group will be calculated. Weight management visit/FTE trends at pre-intervention, baseline, 3, 6, 12 and 18 months post intervention will be plotted to compare the two groups.

The intervention group and control group will be compared using Wilcoxon-Mann–Whitney test. As generalized estimating equation (GEE) can adjust for clustering effect and does not require a normal distribution, we will perform GEE models to compare the 5AsT intervention group and the control group for our primary outcome at 3, 6, 12 and 18 months. Analysis will be by intention to treat.

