**Data Mixing**		
Semi-structured interviews with key providers.	Follow-up of emergent questions.	14-16 months
Semi-Structured interviews with selected patients.	Contextual factors that may have influenced patient behaviors.	18-24 months

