### Qualitative and quantitative data mixing

Qualitative data analysis will be conducted on an iterative base and informs the intervention. The quantitative data for the primary outcome measure, number of weight management visits/FTE, will be collected in a blinded fashion for the first 12 months. At this point, the primary outcome measure will be analyzed. The study team will then be un-blinded and results will be compared with those from the qualitative analysis. It is expected that themes emerging from qualitative data will be reflected in patterns of quantitative data. Any correlation, or lack thereof, will be explored using key informant semi-structured interviews and focus groups. The purpose of this parallel mixed methods design is fourfold: first, to avoid bias during qualitative analysis; second, to explain any variability of the primary outcome measure; third, to record elements of RE-AIM not captured in the quantitative measures for the different providers in the intervention group; and fourth, to monitor the impact of context, and implementation process in part allowing for real-time feedback loops to maximize effective implementation.

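### Practitioners' blinding to the visit results ends at 12 months, while their encounter forms still supply the 18-month comparison and the 12-24 month sustainability data

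*Protocol article*

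**What the plan says.** All references are to the protocol article.

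- **What is counted.** The section Outcome ascertainment, blinding and equal treatment defines the outcome: "The primary outcome measure is the number of weight management visits conducted by the RN/NP participants in their individual practices". On the source: "The primary outcome measure is a routine measure of clinical activity collected on standardized forms within the PCN at every clinical encounter". An audit and quality assurance process for this measure already exists.
- **Why providers are blinded.** Same section: "The provider subjects will be blinded to knowledge of the primary outcome measure so as not to influence their behavior in data collection". No end date is attached to this sentence.
- **How long the results are withheld.** Same section, as a separate statement: "The investigators and health practitioners will have no access to this data and will remain blinded to the results until 12 months following implementation".
- **What happens at 12 months.** Qualitative and quantitative data mixing limits blinded collection to the first 12 months, has the outcome analysed then, and un-blinds the study team. On the fit between visit data and themes it says: "Any correlation, or lack thereof, will be explored using key informant semi-structured interviews and focus groups".
- **When providers are seen again.** Table 2 lists, under Data Mixing, "Semi-structured interviews with key providers" at 14-16 months. Under Sustainability Phase it lists focus groups at 12-24 months.
- **What is still to be measured.** Primary outcomes plans GEE comparisons "for our primary outcome at 3, 6, 12 and 18 months". The 5AsT study overview and the Quantitative statistical analysis plan continue collection through months 12-24, with a second extraction analysed by blinded analysts.
- **The overview's version of the blind.** 5AsT study overview: "Participants are unaware of the primary outcome measure, and the research team is blinded to the result during the study period". It gives no 12-month limit, and the same section counts the sustainability phase as part of the provider study.

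**The concern.** The protocol blinds providers because knowing the measure could change how they collect data. The RN/NPs see prenatal, diabetes, other chronic disease and weight management patients, so how an encounter is booked or classified plausibly leaves room for judgement. That reason applies for as long as the forms feed the outcome, which is to month 24. The results blind stops at month 12, and the follow-up work with providers about the fit of the results begins soon after.

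At stake is whether a visit-count difference at 18 months, or one that persists to 24 months, can be read as sustained practice change rather than changed recording. Provider hypothesis 2 (sustained change) draws on these data. Qualitative data collection takes its participants from those involved in the 5As Team project, so any disclosure through interviews may fall mainly on one arm. It could then be differential.

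**Working it through.** **1. Timeline.** Months are counted from the start of the intervention. The Quantitative statistical analysis plan implies this, because it lists a 12-month assessment and extracts the data after the 12-month intervention and passive period.

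| Month | Event | Section |
|---|---|---|
| 3, 6, 12 | Outcome assessed, practitioners blinded to results | Quantitative statistical analysis plan; Outcome ascertainment |
| 12 | Results blind ends; outcome analysed; study team un-blinded | Outcome ascertainment; data mixing |
| 12-24 | Sustainability focus groups | Table 2 |
| 14-16 | Key-provider interviews | Table 2 |
| 18 | GEE comparison | Primary outcomes |
| 12-24 | Outcome collected for sustainability, then extracted again | 5AsT study overview; Quantitative statistical analysis plan |

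One of the four GEE time points (18 months) and all 12 months of the sustainability phase fall after the results blind ends. The 3-, 6- and 12-month comparisons do not. Primary outcomes words its later time points as post intervention. If its 18 months ran from the end of the six-month Phase 1, it would fall at 6 + 18 = month 24, which is still after the blind ends.

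**2. Two blinds, not one.**

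- Blind to which measure is primary: stated for providers, with no end date.
- Blind to results: stated for investigators and practitioners, ending at 12 months.

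Only the second is lifted in terms. The first is put at risk indirectly, because a practitioner given access to visit results, or asked to explain them, could learn what is being counted. The article does not say how the first blind is to survive the end of the second.

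**3. What protects the later data.** After month 12 the article offers blinded analysts and the routine audit. Blinded analysts protect the analysis but cannot correct a count that was recorded differently. The audit helps, but the protocol judged provider blinding necessary even with the audit in place.

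**4. Scale, as an illustration only.** The documents give no figure for a recording shift, so its size is assumed here.

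Inputs: mean 69.2 and SD 48.1 visits/FTE (Power considerations, provider study); 24 clinics at 1:1, so 12 per arm (Allocation concealment and randomization). A two-sided 0.05 two-sample t-test is assumed, with df = 22 and non-centrality = (difference/SD) × √(12/2).

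- The plan's own figure first: effect size 1.19 gives non-centrality 1.19 × 2.449 = 2.91 and power 79.6%. Using 57/48.1 = 1.185 gives 79.2%. The stated 80% is reproduced.
- The same formula with no true effect and a recording shift across one whole arm:

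| Assumed shift, share of 69.2 | Visits/FTE | Shift/SD | Chance of a false positive |
|---|---|---|---|
| 10% | 6.9 | 0.14 | about 6% |
| 20% | 13.8 | 0.29 | about 10% |
| 30% | 20.8 | 0.43 | about 17% |
| 50% | 34.6 | 0.72 | about 39% |

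Small shifts barely move the error rate and large ones do. The table does not show which is likely. The 69.2 carries no time unit, so the shifts cannot be turned into encounters per month.

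**The case against.** The strongest reply is that the article never says providers will be told the measure or shown their counts. A reader might infer that the whole blind is lifted at month 12 and that the interviews present visit results. The text does not support that:

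- The data-mixing section names only the study team as un-blinded.
- The overview says participants are unaware of the measure, without a time limit.
- Table 2 describes the 14-16-month interviews as following up emergent questions, and the focus groups as covering best practices and impact in the passive phase. Both could be run without naming the measure.

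This stands: disclosure is a risk left open, not a stated procedure. It does not remove the point, because the results blind for health practitioners is expressly limited to 12 months and nothing protects the other blind from then on.

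The reply also notes that the outcome is longstanding administrative data under audit and that the research team does not collect it. That reduces the risk without removing it. The mixing of data at 12 months is a deliberate design choice with stated purposes, and nothing here requires giving it up. RE-AIM also uses interviews and self-reported efficacy, so hypothesis 2 does not rest on visit counts alone.

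Finally, a reader might see the clinical champion's log as another route of disclosure. Table 2 runs that log over months 0-12, so it cannot carry disclosure made after the un-blinding.

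**Conclusion.** The point holds for outcomes after month 12. The results blind on practitioners ends while their encounter forms still supply the 18-month comparison and the sustainability data. The overview's unlimited statement does not agree with the 12-month limit given in the two later sections.

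Two close inferences support it. The first is that RN/NPs complete the forms themselves, which the article implies but does not state. The second is that access to results, or interviews about them, could reveal the measure.

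The size and direction of any bias cannot be derived from the documents. An effect favouring the intervention is possible, because the qualitative work concerns the 5As Team project, but it is not shown. It would also go too far to conclude that the 12-month result is compromised: the 3-, 6- and 12-month comparisons precede the un-blinding. No sample-size or power figure changes.

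**What to change.** 1. In Outcome ascertainment, blinding and equal treatment, and in Qualitative and quantitative data mixing, state that practitioners stay blinded to both the outcome measure and the results until the 24-month extraction.
2. Limit the 12-month un-blinding to the investigators who carry out the data mixing. Data analysts stay blinded to allocation, as the plan already requires.
3. Use interview and focus-group guides at 12-24 months that disclose neither the measure nor visit counts.
4. If disclosure occurs anyway, report the 18-month and sustainability results as unblinded and treat 12 months as the last blinded comparison.
5. Reword the blinding sentence in the 5AsT study overview to agree with the two sections above.

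The change is one of wording and interview conduct. Data mixing at 12 months can go ahead. The cost is that feedback of results to providers, and any interview that quotes those results, waits until after 24 months.
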